| **Administration dose** | 1. **Donafenib** : 200 mg, Bid, to be taken orally starting 3-7 days before the first HAIC treatment; 2. **Sintilimab**: 200 mg, Q3W, intravenous infusion 0-1 days before each HAIC treatment; 3. **HAIC:** FOLFOX regimen hepatic arterial infusion, Q3W, the total number of HAIC treatments will be determined by the investigator based on the patient's actual condition as needed (chemotherapy dose: Oxaliplatin 85 mg/m^2^ infusion over 2 hours, Leucovorin 400 mg/m^2^ infusion over 2 hours, 5-Fu 400 mg/m^2^ bolus over 10 minutes, followed by continuous infusion of 5-Fu 1200 mg/m^2^ over 23 hours);   **Note:**  This study sets a safety lead-in period, during which the first 6 subjects enrolled in the study will undergo gradual safety monitoring. Each patient will receive oral administration of donafenib [200 mg, Bid] in combination with intravenous infusion of sintilimab injection [200 mg, Q3W], along with HAIC treatment. The monitoring window is from the first administration of donafenib treatment to 21±3 days after the first HAIC treatment (i.e., from D1 of the donafenib monotherapy period to C2D1 of the combination therapy period). If ≥2 cases of dose-limiting toxicity (DLT) are observed among the first 6 subjects, and the research team assesses that the toxicity is solely related to donafenib treatment, the initial dose for subsequent enrolled patients receiving donafenib treatment will be adjusted to 100 mg Bid.  During the safety induction period, if a subject does not complete the tolerance observation period (approximately 21±3 days after the first HAIC treatment) due to non-dose tolerance reasons, they will be replaced by a new subject.  After the safety induction period, any enrolled subjects who withdraw from the trial early are not allowed to have additional subjects enrolled as replacements. Furthermore, the corresponding number of the withdrawn subject is not allowed to be reused by other new subjects. |

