| **Dose adjustment scheme** | 1) Donafenib dose adjustment scheme: If grade 4 hematologic toxicity or grade 3 non-hematologic toxicity occurs, temporarily discontinue the drug (according to NCI CTCAE V5.0 standards). After the first suspension of medication, if the adverse reactions recover to ≤ Grade 1 within 1 week, continue taking the original dose; If recovery to ≤ Grade 1 occurs within 2 weeks of suspension, then reduce the dose to 200 mg qd; If the dose is adjusted and medication is suspended again, if recovery to ≤ Grade 1 occurs within 2 weeks, then reduce the dose to 200 mg qod, with a maximum of 2 dose adjustments allowed. If recovery to normal or CTCAE Grade 1 cannot be achieved within 2 weeks after stopping the medication, then permanently discontinue the medication. If Grade 4 hematologic toxicity or Grade 3 non-hematologic toxicity occurs again (the 3rd occurrence), then permanently discontinue the medication.  At an initial dose of 200 mg bid, the dose adjustment scheme is as follows:   \| Initial dose \| First dose reduction \| Second dose reduction \| \| --- \| --- \| --- \| \| 200mg bid \| 200mg qd \| 200mg qod \|   If the initial dose of donafenib is adjusted to 100 mg bid due to the observation of ≥2 cases of DLT in the first 6 patients, the dose adjustment principles will be consistent with those at 200 mg bid, and the specific dose adjustment scheme is as follows:   \| Initial dose \| First dose reduction \| Second dose reduction \| \| --- \| --- \| --- \| \| 100mg bid \| 100mg qd \| 100mg qod \|  1. **Sintilimab dose adjustment scheme**: Dose adjustment of sintilimab is not permitted throughout the study; when intolerable toxicity related to sintilimab occurs, the investigator may decide to suspend or permanently discontinue sintilimab administration.   If a subject experiences a grade 2 drug-related irAE or a grade 3 or higher other AE (refer to the ESMO guidelines for the management of toxicity related to immune checkpoint inhibitors), the subject must suspend the administration of Sintilimab, with a maximum delay of 7 days; the subsequent administration schedule will be adjusted accordingly. If the administration is delayed for more than 7 days, it will be considered a missed dose, and the subject will receive the next cycle of administration according to the original schedule (calculated from the date of the first administration of Sintilimab). If treatment-related adverse reactions have not recovered to grade 0-1 or baseline levels within 6 weeks after the last dose of Sintilimab injection, the administration of Sintilimab injection should be permanently discontinued. Additionally, if the subject discontinues the medication for more than 6 weeks and the investigator determines that the risks of continuing treatment outweigh the benefits, the subject must permanently discontinue Sintilimab.  3) HAIC: In the HAIC chemotherapy regimen, only the dose of Oxaliplatin will be adjusted. That is: when the tumor diameter > 10 cm and there is abundant blood supply, the dose of Oxaliplatin selected is 130 mg/m^2^. For tumors ≤ 10 cm and with less abundant blood supply, the dose of Oxaliplatin selected is 85 mg/m^2^. Additionally, when a large tumor significantly shrinks after several courses of HAIC treatment, a dose reduction may be appropriate, even down to 60 mg/m^2^. Subsequent researchers can make appropriate dose adjustments based on the patient's actual treatment situation and tolerance, and ensure proper documentation.  ***Note**: If a subject permanently discontinues one of the investigational drugs (Donafenib or Sintilimab) due to adverse reactions, and the investigator assesses that the subject may still benefit from continuing the other drug in combination with HAIC treatment, the subject may receive treatment with the other drug in combination with HAIC in this study. If a subject permanently discontinues both drugs due to adverse reactions, the subject must permanently withdraw from the study treatment. |

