## Dose selection basis

### 3.3.1 Donafenib tablets

In this study, the dose of donafenib is 200mg Bid. 200mg Bid is the standard dosing regimen for donafenib in phase III clinical trials for first-line treatment of advanced hepatocellular carcinoma. An exploratory study of 6 patients with advanced gastrointestinal tumors (including 4 cases of liver cancer) treated with 100 mg Bid of donafenib combined with 240 mg Q2W of Sintilimab showed that the overall safety profile of the combination therapy was similar to that of either Sintilimab or donafenib monotherapy, with no unexpected adverse reactions occurring (data not yet published).

This study includes a safety lead-in phase, where the first 6 subjects enrolled in the study will undergo gradual safety monitoring. Each patient will receive oral administration of donafenib tablets [200 mg, Bid] combined with intravenous infusion of Sintilimab injection [200 mg, Q3W], and will receive HAIC treatment on the same day or the following day after Sintilimab infusion. The monitoring window is from the first administration of donafenib treatment to 21±3 days after the first HAIC treatment (i.e., from D1 of the donafenib monotherapy period to C2D1 of the combination therapy period). If ≥2 cases of dose-limiting toxicity (DLT) are observed among the first 6 subjects, and the research team assesses that the toxicity is solely related to donafenib treatment, the initial dose for subsequent enrolled patients receiving donafenib treatment will be adjusted to 100 mg Bid.

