## Dose adjustment/suspension of medication

**donafenib tablets:**

1) The initial dose adjustment scheme is 200 mg bid

During the treatment period, if the subject experiences grade 4 hematologic toxicity or grade 3 non-hematologic toxicity related to the investigational drug, the medication will be temporarily suspended (according to NCI CTCAE V5.0 standards), only allowing the subject to undergo a maximum of 2 dose adjustments. If grade 4 hematologic toxicity or grade 3 non-hematologic toxicity cannot return to normal or CTCAE grade 1 within 2 weeks after suspension, the medication will be permanently discontinued. (Grade 3 or higher adverse reactions do not include alopecia, uncontrolled nausea/vomiting, uncontrolled allergic reactions, and asymptomatic laboratory test abnormalities)

After the first suspension of medication, if the adverse reactions recover to ≤ Grade 1 within 1 week, continue taking the original dose; If recovery to ≤ Grade 1 occurs within 2 weeks of drug suspension, the dose is reduced to 200 mg qd to continue treatment; After dose adjustment, if drug suspension occurs again, and recovery to ≤ Grade 1 occurs within 2 weeks, the dose is reduced to 200 mg qod to continue treatment. If grade 4 hematologic toxicity or grade 3 non-hematologic toxicity occurs again (the 3rd occurrence), the drug will be permanently discontinued. That is Dose adjustment plan:

| Initial dose | First dose reduction | Second dose reduction |
| --- | --- | --- |
| 200 mg bid | 200 mg qd | 200 mg qod |

2) Dose adjustment scheme when the initial dose is adjusted to 100 mg bid due to DLT

If ≥2 cases of dose-limiting toxicity (DLT) are observed among the first 6 subjects, and the research team assesses that the toxicity is solely related to donafenib treatment, then the initial dose adjustment for subsequent enrolled patients receiving donafenib treatment will be 100 mg bid. At this time, the dose adjustment follows the same principles and processes as normal dose adjustments, with specific dose changes as follows:

| Initial dose | First dose reduction | Second dose reduction |
| --- | --- | --- |
| 100mg bid | 100mg qd | 100mg qod |

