2. ECOG PS score collection. If it is conducted within 3 days prior to the first administration, there is no need to repeat the collection on day 1 of the monotherapy period with donafenib ;
3. Investigational drug treatment (donafenib monotherapy);
4. Dispense the treatment drug for the donafenib monotherapy period;
5. Conduct DLT observation after administration: applicable only to patients entering the safety induction phase, i.e., the first 6 patients enrolled;
6. Collect concomitant medication/treatment;
7. Collect adverse events: the adverse events of subjects must be closely monitored throughout the entire research process.
   1. Combination treatment period (the first use of Sintilimab is designated as CIDI, with visits every 3 weeks, time window ±3 days)

After 3-7 days of monotherapy with donafenib , if the subjects are well-tolerated to donafenib during the monotherapy period as assessed by the investigator, subsequent subjects may receive intravenous infusion treatment with Sintilimab injection, and begin approximately 1 day of HAIC treatment on the same day or the day after the infusion of Sintilimab.

All visits during the combination treatment period will be scheduled according to the appropriate calendar days starting from the combination treatment period C1D1 (the day of first use of Sintilimab), with a treatment cycle of every 3 weeks (the length of the 3-week cycle is fixed, regardless of whether the investigational drug is paused). An allowable visit time window of ±3 days is permitted. If at any time during the study the treatment with the investigational drug is paused, all study visits, safety, and efficacy assessments should continue according to the evaluation schedule based on the appropriate calendar days from the combination treatment period C1D1. All data obtained from these assessments must be supported by the original records of the patient. The CRF does not serve as the original record.

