5. Child-Pugh assessment: Once every 3 weeks, with a time window of ±3 days relative to the start of combination therapy on C1D1 ;
6. Evaluate medication adherence from the previous cycle and supplement the necessary donafenib treatment drugs for the next treatment cycle;
7. Conduct DLT observation after administration: applicable only to patients entering the safety induction phase, i.e., the first 6 patients enrolled; The observation and assessment period is: from the first use of donafenib to 21±3 days after the first HAIC treatment;
8. Collect concomitant medication/treatment;
9. Collect adverse events: the adverse events of subjects must be closely monitored throughout the entire research process.

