15. During the monotherapy period of donafenib on Day 1, after calculating the number of doses for the subject based on the determined dosage, the corresponding quantity of medication will be dispensed to the subject. Subsequently, during each combination therapy period on Day 1, there is no need to retrieve any unused medication from the patient; the remaining medication can continue to be taken, and only the quantity of medication required for this treatment cycle needs to be supplemented.
16. After administering the first cycle of donafenib to the subjects on Day 1 of the monotherapy treatment period, subsequent inquiries will be made on Day 1 of each combination treatment period and at the end of the treatment period regarding the amount of medication taken in the previous cycle and the remaining amount in hand, in order to assess whether the patient's medication adherence in the previous cycle meets the requirements;
17. After the first HAIC treatment, the total number of subsequent HAIC treatments will be determined as needed by the investigator based on the actual situation of the subjects;
18. DLT assessment is applicable only to patients entering the safety induction phase of the study (i.e., the first 6 patients enrolled), with the observation and assessment period being: from the first administration of donafenib treatment to 21±3 days after the first HAIC treatment;
19. From 28 days prior to enrollment, all medications/treatments received by the subjects must be recorded in the CRF, including the generic name of the drug, administration dose, frequency, route, the reason for using the drug/treatment, and the start and end dates. Any new changes in medication treatment must be continuously updated;
20. The collection of adverse events (AEs) begins from the signing of the ICF until 30 days after the last administration or the start of a new antitumor treatment, whichever occurs first. Adverse signs, symptoms, or medical conditions that existed at the time of signing the informed consent form should be recorded as medical history;

# Appendix 14

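### If the lead-in lowers the donafenib start to 100 mg bid, no cohort-level DLT count applies to the dose that up to 24 of 30 patients would then receive

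*Protocol*

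**What the plan says.** The Protocol Summary (Administration dose, Note) and section 3.3.1 set up a safety lead-in of the first 6 subjects. "Each patient will receive oral administration of donafenib [200 mg, Bid"], with sintilimab 200 mg Q3W and HAIC. The window runs from the first donafenib dose to 21±3 days after the first HAIC.

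The dose changes if 2 or more of the 6 have a DLT and the research team judges the toxicity to be due to donafenib alone. In that case "the initial dose for subsequent enrolled patients receiving donafenib treatment will be adjusted to 100 mg Bid".

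Three operative places say who is observed for DLT:
- Section 6.2 (donafenib monotherapy period): "Conduct DLT observation after administration: applicable only to patients entering the safety induction phase, i.e., the first 6 patients enrolled".
- Section 6.3 (combination period), item 7: the same restriction, "applicable only to patients entering the safety induction phase, i.e., the first 6 patients enrolled", with the window repeated.
- Attachment 1, note 18: "DLT assessment is applicable only to patients entering the safety induction phase of the study (i.e., the first 6 patients enrolled").

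For the reduced start, the Protocol Summary (Dose adjustment scheme) says that "the dose adjustment principles will be consistent with those at 200 mg bid". Section 5.3 says likewise: "At this time, the dose adjustment follows the same principles and processes as normal dose adjustments". Both then give a ladder for the individual patient: 100 mg qd, then 100 mg qod. Neither mentions a DLT window or a count at 100 mg bid.

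**The concern.** The lead-in exists because the triplet's starting dose is to be checked in six patients before most of the study relies on it. That check lapses in the one branch where it has found a problem. If the dose is reduced, DLT-type events at 100 mg bid would be recorded and could be tabulated afterwards. No rule would oblige anyone to count them across patients while enrolment runs, or to act at a threshold. A cluster would lead to action only through single-patient rules or the investigator's discretion.

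This is a rule of trial conduct that the protocol states expressly. It is not a detail that a statistical analysis plan would normally supply.

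**Working it through.** **Inputs from the protocol.** Fixed sample size 30 (section 3.2); lead-in size 6 and trigger of at least 2 of 6 (section 3.3.1). The protocol gives no DLT rate for this triplet, so every rate below is an assumption. There is no design calculation to reproduce, because the sample size is fixed.

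**Patients affected.** 30 − 6 = 24, and 24/30 = 80%. This is an upper bound. It falls if lead-in replacements count within the 30, or if patients start at 200 mg bid while the lead-in is still being read, since no enrolment hold is stated.

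**How likely the change is.** P(at least 2 of 6) = 1 − (1−p)^6 − 6p(1−p)^5. Take p as the DLT rate at 200 mg bid times the share of DLTs attributed solely to donafenib.

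| DLT rate at 200 mg bid | Half attributed | All attributed |
|---|---|---|
| 20% | p = 0.10: 0.114 | p = 0.20: 0.345 |
| 33% | p = 0.165: 0.259 | p = 0.33: 0.642 |

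**After a change.** The same formula gives the chance that a 2-of-6 count at 100 mg bid is reached. Under the present text that chance is 0 at every rate, because no count applies.

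| Assumed DLT rate at 100 mg bid | Expected DLTs in 24 | P(at least 2 of 6) |
|---|---|---|
| 10% | 2.4 | 0.114 |
| 20% | 4.8 | 0.345 |
| 33% (no improvement) | 7.9 | 0.642 |

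**Limits of six patients.** At a 33% rate the count is missed with probability 1 − 0.642 = 0.358. With 0 of 6 DLTs the one-sided 95% Clopper-Pearson upper limit is 1 − 0.05^(1/6) = 0.393.

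**What the protocol reports about 100 mg bid.**
- Section 1.3.2.1 gives multiple-dose group sizes of 3, 6, 7 and 6 and 5 DLTs. By dose that is 0/3 at 0.1 g, 1/6 at 0.2 g, 1/7 at 0.3 g and 3/6 at 0.4 g. For 0 of 3 the upper limit is 1 − 0.05^(1/3) = 0.632.
- Section 3.3.1 reports 6 patients "treated with 100 mg Bid of donafenib combined with 240 mg Q2W of Sintilimab", with safety similar to either drug alone and no unexpected reactions. HAIC is not mentioned.
- No patient on the triplet at 100 mg bid is reported.

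**The case against.** The strongest reply is that this is a step down, not an untested escalation. The 200 mg bid dose is the phase III regimen, and donafenib is approved for first-line advanced liver cancer (section 5.4.1). The reduction happens only after the toxicity has been attributed to donafenib alone, and that drug is then halved. The 33% scenario is therefore the least plausible. This stands, and it is why the point is modest.

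A reader might infer from the steady-state data that halving the dose would not help. Section 1.3.2.1 does report no significant change in steady-state exposure over 0.1 to 0.4 g, and in section 1.3.2.2 AUCss rises only 58.9/46.7 = 1.26-fold for a 1.5-fold dose. The documents do not support that inference:
- The phase I groups are very small, with considerable variability between subjects.
- Single-dose exposure rose roughly in proportion to dose.
- The second comparison covers 0.2 g against 0.3 g, not 0.1 g. Its accumulation factors imply day-1 AUCs of 46.7/4.99 = 9.4 and 58.9/3.10 = 19.0, about a doubling.
- DLTs clustered at the highest dose.

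A reader might also infer that patients at 100 mg bid would be without safety oversight. They would not. Tolerance is checked after the donafenib-only days and before each cycle from C2D1 (section 6.3). Individual hold and stop rules apply (section 5.3). All adverse events are graded and recorded (section 8.7.1), and serious ones are reported within 24 hours (section 8.7.2). The investigator may terminate the study for unacceptable risk (section 4.3.1). At a single centre, one team sees every patient. None of these sets a count across patients, so the narrower gap remains.

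**Conclusion.** The point holds in limited form. If the lead-in triggers the reduction, the protocol as written excludes any cohort-level DLT count for the starting dose of up to 24 of 30 patients.

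Its weight is modest. It needs at least 2 DLTs in 6 and sole attribution to donafenib. Under the assumed rates, that has a probability of 11–26% if half of DLTs are so attributed and 34–64% if all are. Lower toxicity than at 200 mg bid is likely, but 0 of 3 on monotherapy and six doublet patients do not establish it for the triplet.

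A mandatory enrolment hold until six windows are complete might seem to follow, but the protocol's own standard does not require it. It states no such hold for the lead-in at 200 mg bid. One window lasts 3 + 0 + 18 = 21 to 7 + 1 + 24 = 32 days, so a hold would be a debatable trade-off at the lower dose.

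**What to change.** 1. In the Protocol Summary (Administration dose, Note) and section 3.3.1, add: *If the starting dose is changed to 100 mg bid, the first 6 DLT-evaluable patients at that dose undergo the same DLT observation (same window, definitions and replacement rule). If a second DLT occurs among them, no further patient starts treatment until a documented safety review under 4.3.1 has decided whether to continue.*
2. In section 6.2 (item 5), section 6.3 (item 7) and Attachment 1, note 18, extend the restriction to the first six patients with: *and, if the starting dose is changed, the first 6 DLT-evaluable patients at 100 mg bid*.

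This changes wording in five places and relies on adverse event and laboratory data already collected by C2D1. It costs nothing unless the dose is changed. In that case it costs DLT adjudication in 6 more patients and a short pause for review, with probability about 11% at a 10% DLT rate and 34% at 20%. DLTs due to HAIC or sintilimab would also count, so a review may be called for reasons other than donafenib. Without a hold, the number of patients not yet exposed when a review is called depends on accrual speed, which the protocol does not give.

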## End of treatment visit (confirmation of end/discontinuation of treatment within 7 days)

1. Safety data: Collection items are the same as during the treatment period; if the urine pregnancy test result cannot be confirmed as negative, a serum pregnancy test must be conducted, with the serum pregnancy result being definitive;
2. AFP testing;
3. CT/MRI examination;
4. ECOG PS score collection.
5. Evaluate medication adherence from the previous cycle;
6. Collect concomitant medication/treatment;
7. Collect adverse events.

If a patient stops treatment during a study visit, there is no need to repeat the treatment termination visit assessment.

## Follow-up period (every 12 weeks, with a window of ±7 days)

### Safety follow-up

Subjects who complete treatment with the investigational drug will enter the follow-up period, recording all adverse events and concomitant medications for 30 days (±7 days) after the last administration or before receiving new antitumor therapy (whichever occurs first), as well as all new antitumor therapies after the last administration. For all adverse events or subjects who discontinue study treatment due to laboratory abnormalities, follow-up must be conducted until the event resolves or returns to baseline or better, the investigator confirms the event is stable, the subject withdraws consent, or the subject is lost to follow-up, and the results must be recorded in the CRF. Every effort should be made to follow up on all serious adverse events deemed related to the investigational drug or study-related procedures until a final outcome can be reported.

